### Statistical analysis

PFS has been set as the primary endpoint and is defined as the time from date of registration until the date that progression is determined or the date of death for any reason, whichever is sooner. “Progression” will be evaluated on the basis of Response Evaluation Criteria In Solid Tumors (RECIST) version 1.1
[17]. More information about the definition of PFS and Progression are pre-specified (Table
1).

**Table 1 T1:** Definition of PFS and progression

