8.)	In cases where progression is diagnosed on the basis of imaging, the event will be determined based not on evaluation dates where the result is “suspected” on imaging but on a subsequent evaluation date where progression is “confirmed” on imaging.
9.)	Secondary cancer (multiple cancers in metachronous) will not be regarded as either an event or censored.

The primary objective of this trial is to evaluate the PFS of SP and XP as the first-line treatment for advanced gastric cancer. The 24-week progression-free rate (PFR) will be estimated for each group, calculating point estimates and 2-sided 90% confidence intervals. The 2-sided 90% confidence interval of the difference between the 2 groups will be also estimated. Exploratory analysis will be done to test the null hypothesis that PFS is equal in both groups. Cumulative PFS curves will be constructed as time-to-event plots by the Kaplan-Meier method.

With respect to secondary endpoints, efficacy endpoints OS and TTF will be evaluated according to the method of analysis of the primary endpoint. Overall response rate (RR) is defined as the proportion of patients with complete response (CR) or partial response (PR) by RECIST out of the patients with measurable lesions, and the chi-square test will be used to compare the 2 groups. The 2-sided 95% confidence interval of the difference between the 2 groups will also be estimated. For the analysis of safety, Fisher’s exact test will be used if necessary, and the exact confidence intervals for the binomial distribution will be estimated.

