### Sample-size calculation

Assuming a threshold 24-week PFR of 40% and an expected 24-week PFR of 55% (clinically promising), and a 1.5-year registration period and a 1.5-year follow-up period, 49 patients are required in each group to ensure a 1-sided alpha of 5% and statistical power of 90%. Assuming that the 24-week PFR of the biomarker-positive (any FU-related enzyme or expression of intestinal type) population in the SP arm is 45%, and the risk reduction rate in the XP arm is 40%, 46 patients in total are needed to ensure a 2-sided alpha of 10% and statistical power of 70%. Under the hypothesis that the targeted biomarker-positive population is 50%, 92 patients in total are required. Considering the likelihood of some ineligible cases in the whole setting outlined above, the total sample size is set to 100. A following Phase III study will be designed for both randomized comparison and biomarker-oriented comparison of XP and SP (4 groups).

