## Discussion

Recently, molecular target drugs has resulted in the opportunity to provide individualized treatment in the field of AGC. Especially in patients with HER2-positive AGC (defined as assessed by IHC 3+ on a scale of 0 to 3+, and/or fluorescence in-situ hybridization; FISH, *HER2*:CEP17 ratio ≥2.0), ToGA study showed that adding trastuzumab was significantly improved overall survival comparing with standard chemotherapy consists of cytotoxic drugs
[11]. This study excludes HER2-positive gastric cancer since these patients should be recommended trastuzumab containing regimen. The individualized treatment for cytotoxic agents also needs to be developed to have more effect and less toxicity.

This is the first study to compare two standard regimens for AGC. Additionally, the translational research is performed to explore the biomarker for chemo-sensitivity and make the individualized treatment possible. When the difference of treatment is found in efficacy or safety from this analysis, we will conduct a phase III trial to examine the possibility of individualized treatment. We believe the result of this study will play the important role to prepare the individualized therapy for advanced gastric cancer in the near future.

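### The only XP-versus-SP effect estimate stated for PFS is the difference in 24-week rates, an inefficient contrast; a hazard ratio over all follow-up with its 90% interval should lead instead

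*Protocol article*

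**What the plan says.** All of this is in the protocol article.

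- **Endpoint** (opening of the Statistical analysis section): "PFS has been set as the primary endpoint and is defined as the time from date of registration until the date that progression is determined". Death counts as the event if it comes sooner. It is a time-to-event measure.
- **Per-arm summary** (Statistical analysis, after Table 1): "The 24-week progression-free rate (PFR) will be estimated for each group, calculating point estimates and 2-sided 90% confidence intervals".
- **Between-arm estimate** (next sentence): "The 2-sided 90% confidence interval of the difference between the 2 groups will be also estimated". In context this is the difference in 24-week PFR.
- **Comparison over all follow-up** (next sentence): "Exploratory analysis will be done to test the null hypothesis that PFS is equal in both groups". Kaplan-Meier curves are also planned. No hazard ratio or other whole-curve effect measure is named.
- **OS and TTF** are to follow the method used for the primary endpoint.
- **Sample-size calculation**: 24-week PFR of 40% (threshold) and 55% (expected), "a 1.5-year registration period and a 1.5-year follow-up period", 49 patients per group for a 1-sided 5% level and 90% power, and 100 patients in total. No power is stated for XP against SP in all patients. The only between-arm sizing concerns the biomarker-positive patients.

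**The concern.** The trial compares two regimens on a time-to-event endpoint, yet the one between-arm effect it will report with an interval is read off the curves at a single time. Progressions and deaths after week 24 do not enter that estimate. Neither does the timing of events before week 24. A bare test of equality, labelled exploratory, uses those events but gives no effect size or interval.

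At stake is the precision with which XP and SP are compared. With 50 patients per arm, a 24-week difference is coarse, and data already being collected would support a sharper estimate. Because OS and TTF follow the same method, the choice may carry over to them.

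**Working it through.** **Inputs.** From the article: PFR 40% and 55% at 24 weeks, 50 per arm, accrual a = 1.5 years, follow-up f = 1.5 years, 90% intervals (2-sided 10%, z = 1.645). Assumed: exponential PFS, uniform accrual, and 40% and 55% as the two arms' true rates.

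**1. The plan's own 49 per group.** With t = 24 weeks = 0.46 years, λ = −ln(PFR)/t gives 1.992 and 1.300 per year, so HR = ln 0.55 / ln 0.40 = 0.652 and ln HR = −0.427. The chance of an observed event is 1 − [exp(−λf) − exp(−λ(a+f))]/(λa), which is 0.984 and 0.937.
- One-sample exponential test: events = (1.645 + 1.282)²/0.427² = 47.0, and 47.0/0.937 = 50.1 patients. The mean-survival form gives 47.9. Power at n = 49 is 89.4%. The stated 49 is reproduced approximately.
- One-sample test of the 24-week proportion: (1.645√0.24 + 1.282√0.2475)²/0.15² = 92.6, so 93 patients. This does not give 49.

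The sizing therefore appears to count events over the whole follow-up.

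**2. Difference in 24-week PFR.** SE = √(0.40×0.60/50 + 0.55×0.45/50) = 0.0987. The 90% half-width is 1.645 × 0.0987 = 0.162, about 16 points, which is wider than the 15-point difference. Power = Φ(0.15/0.0987 − 1.645) = 45.0% (44.3% with pooled variance).

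**3. Log-rank over all follow-up.** Expected events = 50 × (0.984 + 0.937) = 96.1. Power = Φ(½√96.1 × 0.427 − 1.645) = 67.3%. The gap to step 2 is about 22 points.

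**4. Events outside the 24-week contrast.** By week 24: 50 × (0.60 + 0.45) = 52.5. After: (96.1 − 52.5)/96.1 = 45%. A log-rank test restricted to those 52.5 events has power 46.1%, so nearly all of the gap comes from the later events.

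**5. Precision on a common scale.** The half-width for ln HR is 1.645 × 2/√96.1 = 0.336. Multiplying by |S ln S| at S = 0.475 to 0.55 (0.354 to 0.329) gives about 11.9 to 11.0 points, against about 16.

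**6. Sensitivity.**

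| Inputs | 24-week difference | Log-rank | Events after week 24 |
|---|---|---|---|
| 40% vs 55%, formulas above | 45% | 67% | 45% |
| Same, 10,000 simulated trials | 43% | 67% | 45% |
| Same, assumed extra censoring of 15% per 24 weeks, simulated | 43% | 60% | 39% |
| 45% with HR 0.6 (0.45^0.6 = 62%), 50 per arm | 53% | 79% | 50% |

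The last row takes the article's biomarker-positive assumptions, reads the 40% risk reduction as a hazard ratio, and applies them to all 100 patients. The article makes no such assumption, so the row only tests the direction. In simulation with equal arms, rejection was 11.0% for the 24-week difference and 10.7% for the log-rank test, so the gap does not come from differing error rates.

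**The case against.** The strongest reply is that nothing in the article makes the 24-week difference the main comparison. The objective is estimation, arm by arm, and the between-arm interval is an addition. A whole-curve test and Kaplan-Meier curves are planned as well. Per-arm estimation with an exploratory comparison is a coherent phase II design. This stands in large part. A reader might infer that late events are ignored or that planned power is lost. The documents support neither: late events enter the test and the curves, and no all-patient between-arm power is stated from which anything could be lost.

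A reader might also infer that the phase III decision hangs on the 24-week difference, because the Discussion says "When the difference of treatment is found in efficacy or safety from this analysis, we will conduct a phase III trial". That sentence follows one on translational research, names efficacy or safety without any 24-week criterion, and describes a phase III trial about individualized treatment. It does not support that inference.

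The size of the gap is also open to challenge. The 40% and 55% are per-arm design values, not SP against XP. Table 1, item 7, censors patients who stop for toxicity or refusal, which narrows the gap.

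The biomarker-positive sizing of 46 patients may itself reflect a whole-curve comparison. If the 40% reduction is applied to the 55% risk of progression or death by week 24 (45% against 67%, HR 0.50), a log-rank calculation needs about 43 patients (Schoenfeld) or 47 (Freedman). Read as HR 0.6, it needs about 78 by Schoenfeld. Where it fits, this favours the change, because the sizing and the stated analysis would then use the same kind of comparison.

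Finally, a hazard ratio may sit in a full protocol or SAP that is not shown, so its absence alone is no finding. What remains is the ordering that the article does state: the 24-week difference gets an interval, and the whole-curve comparison is an exploratory test. Proportional hazards are also not assured, since the Background expects effects to vary with histology and enzyme expression.

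**Conclusion.** The point holds as an efficiency improvement. The stated between-arm PFS estimate is less efficient than the collected data allow. Power is about 45% against about 67% if the true 24-week rates are 40% and 55%, PFS is exponential, there are 50 patients per arm and the level is 2-sided 10%. The gap of about 22 points falls to about 16 to 17 with assumed extra censoring of 15% per 24 weeks. Across the scenarios shown, about 39% to 50% of PFS events do not enter the 24-week contrast, and its 90% half-width is about 16 points. The direction is the same in every scenario, and all of them assume proportional hazards.

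This is not an error in a stated power or sample size, and it says nothing against the per-arm assessment at 24 weeks.

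**What to change.** In the Statistical analysis section:

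- Name the PFS hazard ratio over all follow-up, with its 2-sided 90% confidence interval, as the leading between-arm PFS estimate, with the log-rank test beside it.
- Keep the 24-week PFR with 90% interval in each arm for the 40%/55% assessment.
- Report the difference in 24-week PFR as supportive, and use it to describe the effect if hazards are clearly non-proportional.
- Say whether the same ordering applies to OS and TTF, which follow the primary endpoint's method.

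The cost is a few sentences, with no extra patients, visits or data. The downside is that the hazard ratio relies on roughly proportional hazards. The 24-week rates and Kaplan-Meier curves already planned are the safeguard.

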### Sample-size calculation

Assuming a threshold 24-week PFR of 40% and an expected 24-week PFR of 55% (clinically promising), and a 1.5-year registration period and a 1.5-year follow-up period, 49 patients are required in each group to ensure a 1-sided alpha of 5% and statistical power of 90%. Assuming that the 24-week PFR of the biomarker-positive (any FU-related enzyme or expression of intestinal type) population in the SP arm is 45%, and the risk reduction rate in the XP arm is 40%, 46 patients in total are needed to ensure a 2-sided alpha of 10% and statistical power of 70%. Under the hypothesis that the targeted biomarker-positive population is 50%, 92 patients in total are required. Considering the likelihood of some ineligible cases in the whole setting outlined above, the total sample size is set to 100. A following Phase III study will be designed for both randomized comparison and biomarker-oriented comparison of XP and SP (4 groups).

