**Methods/design:**

This is a multicenter randomized phase II trial to elucidate the efficacy of XP as compared with SP for first-line treatment of advanced gastric cancer. Patients with unresectable metastatic or recurrent gastric cancer, 20–74 years of age and human epidermal growth factor 2 (HER2)-negative status, will be assigned in a 1:1 ratio to receive either S-1 40 mg/m^2^ bid for 21 days plus cisplatin 60 mg/m^2^ (day 8) every 5-week cycle or capecitabine 1000 mg/m^2^ bid for 14 days plus cisplatin 80 mg/m^2^ (day 1) every 3-week cycle. Patients will be also asked to the analysis of tumor tissues for translational investigations. The Primary endpoint is progression-free survival and secondary endpoints are overall survival, time to treatment failure, tumor response rate and safety. These comparisons will also be evaluated in terms of biomarkers. Planned sample size is 100 (50 in each arm), which is appropriate for this trial.

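### The stated 90% power at 49 per arm fits a whole-curve exponential test, not the planned 24-week PFR with a 90% CI, which has about 66–69% power

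*Protocol article*

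**What the plan says.** Under Sample-size calculation, the hypothesis is put in terms of the 24-week PFR: "Assuming a threshold 24-week PFR of 40" per cent and "an expected 24-week PFR of 55% (clinically promising"), together with "a 1.5-year registration period and a 1.5-year follow-up period". From these inputs the protocol concludes that "49 patients are required in each group to ensure a 1-sided alpha of 5% and statistical power of 90" per cent. After an allowance for ineligible cases, "the total sample size is set to 100"; the Abstract gives the split: "Planned sample size is 100 (50 in each arm").

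Under Statistical analysis, the text following Table 1 gives the analysis for the primary objective: "The 24-week progression-free rate (PFR) will be estimated for each group, calculating point estimates and 2-sided 90% confidence intervals". A 90% interval for the difference between arms is added, and Kaplan-Meier curves are to be drawn. The test between arms has a lesser status: "Exploratory analysis will be done to test the null hypothesis that PFS is equal in both groups". Neither section mentions an exponential model, a one-sample log-rank test or any other whole-curve test against the 40% threshold.

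**The concern.** The two sections look built to match: the lower limit of a two-sided 90% interval is a one-sided 5% bound, so a per-arm test of the 40% threshold reads naturally as asking whether that limit lies above 40%. But 49 patients are far too few to detect 55% against 40% with 90% power on a proportion at one fixed time.

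The accrual and follow-up periods are a clue. With at least 1.5 years of follow-up, administrative censoring cannot occur before week 24, so those periods are irrelevant to an estimate at week 24. They matter only for a test that counts events over the whole study. The sample size therefore appears to come from a test that uses every event time, while the analysis section describes an estimate that ignores when progression occurs before week 24 and everything after it.

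At stake is the power of the primary per-arm result. A regimen at the level the protocol calls promising would fail to clear the threshold much more often than a reader of the sample-size section would expect.

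**Working it through.** **Inputs.** From Sample-size calculation: p0 = 0.40, p1 = 0.55, one-sided alpha 0.05 (z = 1.645), power 0.90 (z = 1.282), accrual 1.5 years, follow-up 1.5 years, n = 49 per arm. From Statistical analysis: 24-week PFR with a two-sided 90% interval. From the Abstract: 50 enrolled per arm.

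**Step 1: reproduce 49.** Assume exponential PFS and uniform accrual, with 24 weeks = 24/52 year.

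- Hazards per year: h0 = −ln(0.40)/(24/52) = 1.985; h1 = −ln(0.55)/(24/52) = 1.295.
- Hazard ratio: ln(0.55)/ln(0.40) = 0.652; its log is −0.427.
- Event probability: 1 − [exp(−1.5h) − exp(−3h)]/(1.5h), which gives 0.984 under the threshold and 0.937 under the alternative.
- One-sample test on the log hazard: n = [(1.645/√0.984 + 1.282/√0.937)/0.427]² = **48.8, rounded up to 49**.

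Close variants of the same test land nearby: 47.7 with the null variance only, 50.1 with the alternative variance only (47.0 events divided by 0.937), 47.9 on the mean scale, 49.7 on the cube-root scale and 52.7 on the hazard scale. A one-sample log-rank formula gives 56.6, but simulated power for that test is already about 89% at n = 49.

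**Step 2: try the fixed-time formulas.** For a one-sample proportion:

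n = [(1.645·√(0.40×0.60) + 1.282·√(0.55×0.45))/0.15]² = [(0.806 + 0.638)/0.15]² = **92.6, so 93**.

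Other fixed-time versions give 91.3 (null variance only), 94.2 (alternative variance only, and arcsine), 93.9 (complementary log-log), 95.8 (logit) and 99.3 (log). Exact binomial gives 94 (at least 46 of 94; alpha 4.9%, power 90.0%). A two-arm comparison of 40% with 55% needs 188 per arm. None of these is near 49.

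**Step 3: power of the described analysis at n = 49.**

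- Exact binomial: the lower limit exceeds 40% when at least 26 of 49 are progression-free. Actual alpha is 4.4% and power at 55% is **66.3%**. Wald, Wilson and Clopper-Pearson limits all give this same cut-off at 49.
- Normal score: Φ[(7×0.15 − 0.806)/0.497] = Φ(0.491) = **68.8%**.
- Simulated Kaplan-Meier estimate with its 90% interval, no censoring before week 24: about 66%.

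**Step 4: the 50 enrolled per arm.** Discreteness makes the result depend on the interval.

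| Interval at n = 50 | Cut-off | Actual alpha | Power |
|---|---|---|---|
| Clopper-Pearson (exact) | 27/50 | 3.1% | 61.3% |
| Wald or Wilson | 26/50 | 5.7% | 71.6% |

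The higher figure exceeds the stated 5% level. The normal approximation gives 69–70%.

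**Step 5: power of the whole-curve test.** By formula (alternative variance), power at 49 is Φ[√(49×0.937)×0.427 − 1.645] = Φ(1.25) = 89.4%, and at 50 it is 89.9%. Simulation of the one-sample log-rank test gives about 89% at both sizes.

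**Step 6: early censoring.** Table 1, items 3 and 7, censors clinical progression without objective evidence and discontinuation for toxicity or refusal. No rate is stated. With an assumed 5–20% censored independently by week 24, simulated power of the Kaplan-Meier analysis at 49 is 59–67%.

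**The case against.** The strongest reply is that 49 is not miscalculated. It is correct for a recognised method, and the stated accrual and follow-up periods point to that method. The primary endpoint is PFS as a time to event, not a binary status at week 24. The analysis section names Kaplan-Meier only for the curves, so a 24-week PFR estimated from an exponential model would also fit its wording and would have roughly the stated power. The choice of estimator could sit in an analysis plan that is not at hand.

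Second, no rule is written that the lower limit must exceed 40%, and the Discussion ties the phase III decision to a difference between treatments, not to either arm clearing a threshold. The total of 100 also has separate support from the biomarker calculation (92 patients).

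Part of this stands. The fault is a mismatch between the sizing method and the described analysis rather than a slip of arithmetic. The sizing formula and the lower-limit rule are both inferred. The confidence intervals remain valid, and the biomarker calculation still supports about the same total.

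It does not rescue the 90%. A threshold, an alpha and a power imply a test, and the 90% interval is the only per-arm inference offered. Read in the ordinary, nonparametric way, that analysis has about two-thirds power wherever 49 came from. If a model-based estimate or another test was intended, the power statement belongs to an analysis the protocol does not describe, and one sentence is still needed to say so.

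**Conclusion.** The concern holds. The stated 90% power does not belong to the primary analysis as described. At 49 per arm, the 24-week PFR with its lower 90% limit compared with 40% has 66.3% power (exact) to 68.8% (normal approximation). At 50 per arm it has about 61–72%, depending on the interval. The chance that a regimen truly at 55% misses the threshold is therefore about one in three, against the one in ten implied. About 93–94 evaluable patients per arm would be needed for 90%.

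These figures assume that the 24-week PFR is estimated without a parametric model, that the decision is the lower limit exceeding 40%, and that 24-week status is known for essentially all patients. Early censoring tends to lower the power further. The attribution of 49 to a one-sample exponential test is an inference from its reproducing the number with the protocol's own inputs; the shortfall does not depend on it.

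**What to change.** Make one of two changes before the data are analysed, so that the test is not chosen after results are seen.

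- **(a)** Keep the 24-week PFR with its 90% interval as the primary per-arm analysis. State the interval method and the lower-limit criterion, and restate the power as about 66–69% with 49 evaluable patients per arm (about 61–72% at 50, depending on the interval). The cost is a less favourable stated power.
- **(b)** Name the test that was sized as the primary per-arm test: an exponential-model estimate, or a one-sample log-rank test, against the curve with a 24-week PFR of 40%. Declare the exponential shape and report the Kaplan-Meier 24-week PFR as supportive. This keeps about 89–90% power at 49–50 per arm, at the cost of relying on the assumed shape of the reference curve.

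Either is a sentence in the Sample-size calculation or Statistical analysis section, and neither needs extra patients. Keeping both the described analysis and 90% power would instead require about 93–94 evaluable patients per arm, before any allowance for ineligible cases.

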### Eligibility criteria

#### Inclusion criteria

(i) Histologically confirmed gastric adenocarcinoma with unresectable metastatic or recurrent disease

(ii) Lesions confirmed by imaging no more than 28 days before registration (not required for measurable lesions as defined in RECIST version 1.1)

(iii) No previous chemotherapy or radiotherapy. However, prior adjuvant chemotherapy is allowed if more than 6 months has passed since the end of adjuvant chemotherapy

(iv) Eastern Cooperative Oncology Group (ECOG) Performance Status of 0, 1, or 2

(v) Life expectancy of at least 3 months after registration

(vi) Written informed consent

(vii) Between the ages of 20 and 74 years at the time informed consent is obtained

(viii) Adequate major organ function including:

(a) Neutrophil count: ≥1500/mm^3^

(b) Platelet count: ≥10.0 × 10^4^/mm^3^

(c) Hemoglobin: ≥9.0 g/dL

(d) AST, ALT: ≤2.5 × upper limit of normal (ULN) in each institution (≤5 times in cases of metastases to liver)

(e) ALP: ≤2.5 × ULN in each institution (≤5 times in cases of metastases to liver, and ≤10 times in cases of metastases to bone)

(f) Total bilirubin: ≤1.5 × ULN in each institution

(g) Creatinine clearance: ≥60 mL/min (as estimated by Cockcroft-Gault equation)

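### The enzyme-marker sizing divides by prevalence alone, with no allowance for unevaluable tissue, and its 70% power is not reached on the stated inputs at any evaluable fraction

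*Protocol article*

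**What the plan says.** The Sample-size calculation section of the Protocol article has a second sizing, for a biomarker-positive population. Positivity may rest on an FU-related enzyme or on intestinal histology. The assumed 24-week progression-free rate and effect are given as "population in the SP arm is 45%, and the risk reduction rate in the XP arm is 40" (per cent). From these it concludes that "46 patients in total are needed to ensure a 2-sided alpha of 10% and statistical power of 70" (per cent).

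The conversion to trial size follows: "Under the hypothesis that the targeted biomarker-positive population is 50%, 92 patients in total are required". The last step is: "Considering the likelihood of some ineligible cases in the whole setting outlined above, the total sample size is set to 100".

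On tissue, the abstract (Methods/design) says: "Patients will be also asked to the analysis of tumor tissues for translational investigations". The Translational research project section says that samples will be collected and assessed centrally, by immunohistochemistry and mRNA expression, but gives no expected rate. The nearest entry condition is inclusion criterion (i), "Histologically confirmed gastric adenocarcinoma with unresectable metastatic or recurrent disease". No printed inclusion or exclusion criterion requires tissue to be available for the marker assays, or consent to that use. Intestinal or diffuse histology is a balancing factor at randomisation, so it must be recorded for every patient.

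**The concern.** Dividing the required number of positives by the prevalence is correct only when marker status is known for everyone counted. For TP, DPD and the other enzymes it depends on a usable specimen and a successful assay. The calculation has no factor for that, and its only margin is reserved for another kind of loss.

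The enzyme markers are central to the trial's rationale, and the section names a biomarker-oriented phase III as the next step. A reader planning that trial would take from this section that the enzyme comparison has 46 positives and 70% power. If the evaluable number is smaller, or if 46 never gave 70%, a negative or unstable biomarker result would be given more weight than it can bear.

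**Working it through.** **Inputs from the Sample-size calculation section.** 24-week progression-free rate of 45% in the SP arm; 40% risk reduction with XP; 2-sided alpha 10%; power 70%; 46 positives in total; prevalence 50%; total 100; "a 1.5-year registration period and a 1.5-year follow-up period". Allocation is 1:1 (abstract). The evaluable fraction f is not given and is varied below.

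**Step 1: the plan's 92.** 46/0.50 = 92. This reproduces exactly and leaves no room for unevaluable tissue.

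**Step 2: evaluable fraction needed for 46 positives.** Expected evaluable positives among 100 patients are 100 × f × 0.50. Setting this to at least 46 gives f ≥ 46/50 = 0.92. If the 8 patients above 92 are lost as ineligible, 92 × f × 0.50 ≥ 46 gives f = 1.00. Even f = 0.92 gives 46 only on average: with 100 patients and a probability of 0.46 of being evaluable and positive, the binomial chance of at least 46 is about 54%.

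**Step 3: does 46 give 70%?** Read the 40% risk reduction as a hazard ratio of 0.60 and use the Schoenfeld formula for a 1:1 log-rank comparison:

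events = 4 × (1.645 + 0.524)² / (ln 0.60)² = 4 × 4.706 / 0.2609 ≈ 72.1, so 73.

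The Freedman formula gives 76. Forty-six patients cannot supply 73 events, so the stated 46 is not reproduced under this reading, whatever the follow-up. If all 46 had an event, power would be Φ(√46 × 0.5108/2 − 1.645) = Φ(0.087) ≈ 53%.

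**Step 4: patients needed.** Assume exponential PFS, uniform accrual, and that the 1.5 + 1.5 years stated for the primary sizing also apply here. The SP hazard is −ln 0.45 / (24/52.18) ≈ 1.736 per year, and the XP hazard is 0.60 × 1.736 ≈ 1.042. The event probabilities are 0.974 and 0.894, mean 0.934. Then 73/0.934 gives 79 marker-positive patients (82 with Freedman), or about 158 to 164 overall at 50% prevalence.

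**Step 5: power at N = 100.** Events = positives × 0.934; power = Φ(√events × 0.5108/2 − 1.645).

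| Evaluable fraction (assumed) | Expected positives | Expected events | Power |
|---|---|---|---|
| 100% | 50 | 46.7 | 54% |
| 92% | 46 | 43.0 | 51% |
| 80% | 40 | 37.4 | 47% |
| 70% | 35 | 32.7 | 43% |
| 50% | 25 | 23.3 | 34% |

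A simulated log-rank test under the same assumptions gave 50% power with 23 per arm and 53% with 25 per arm, in line with the formula.

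**Step 6: other readings of the inputs.** A one-sided 10% test with hazard ratio 0.60 needs 50 events and 54 patients. If the 40% is applied to the failure proportion at 24 weeks, the comparison is 45% against 1 − 0.55 × 0.60 = 67%. At 2-sided 10% that needs 46 to 57 patients per arm, depending on the formula; with 23 per arm power is about 44%. None of these gives 46 in total.

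**The case against.** The strongest defence has four parts.

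First, this is a condensed article. Rules on tissue consent and submission commonly sit in the full protocol. The abstract says patients are asked, but it does not say that refusal leaves them eligible, and the Translational research project section says samples will be collected. HER2-positive patients are excluded, and the Discussion describes HER2 assessment by immunohistochemistry and in-situ hybridisation, so some tumour material should exist for nearly everyone. This stands in part. A reader might infer that a shortfall in tissue is likely, but no rate is given and the documents do not support that. The point that survives is narrower: the published calculation is complete in itself, names its only allowance, and has no term for evaluability.

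Second, intestinal type counts as a positive marker and is known for all patients. This stands, and it limits the point to the enzyme markers. If positivity is meant as a composite of enzyme or histology, an intestinal-type patient without usable tissue is still positive, and the table overstates the loss.

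Third, a reader might infer that 92% evaluable would deliver the stated 70%. The stated inputs do not support that: power is about 51% there and about 54% with no tissue loss at all. The figure of 46 is the larger problem, and a tissue allowance alone would not repair it. It is also tempting to say that 46 is a per-arm figure labelled as a total, because the unpooled two-proportion formula for 45% against 67% gives 45.6 per arm. The article does not name its method, so this is only a possible explanation.

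Fourth, the biomarker aim is exploratory and is not among the endpoints. This stands as a limit on the consequences. The progression-free survival sizing of 49 per group does not depend on tissue.

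**Conclusion.** The point holds for the enzyme markers. The step from 46 to 92 assumes complete marker data, the 8 spare patients are assigned to ineligibility, and the printed criteria do not secure tissue. The expected count of 46 needs 92% to 100% evaluable, depending on how many of the spare patients prove ineligible.

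Separately, the 70% is not attained at any evaluable fraction with 100 patients. At 50% prevalence the most the design offers is about 54%.

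The power figures rest on a hazard ratio of 0.60, exponential PFS, uniform accrual and the primary sizing's accrual and follow-up periods. That 46 patients are too few under that hazard ratio does not depend on the last three, because 73 events exceed 46 patients. The evaluable fraction is an assumption throughout; an actual tissue shortfall is possible but not shown.

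**What to change.** In the Sample-size calculation section, replace the statement that "46 patients in total are needed to ensure a 2-sided alpha of 10% and statistical power of 70" (per cent), and the conversion to 92, with three items:

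- the evaluable fraction the sponsor expects for the enzyme markers, and its basis;
- the expected number of evaluable marker-positive patients at N = 100, and the power recomputed from the stated inputs with the method named. For example, at an assumed 80% evaluable and 50% positive: 40 patients, about 37 events, power about 47% at 2-sided 10%;
- a sentence saying that the intestinal-type comparison is not affected by tissue availability.

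The cost is a less favourable published power for an exploratory comparison. No added enrolment is needed. A new tissue criterion is not needed either: enrolment began in July 2011, so it would apply only to later patients, and it would not prevent assay failures.
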